**4.10 Information on the Proposed Data Analysis**

All analyses will follow the intention-to-treat principle.

Primary outcome (FIQR). Intervention effects will be assessed using a two-way repeated-measures ANCOVA with one within-subject factor (Time: t0, t1) and one between-subject factor (Group: IVR+exercise vs exercise). The dependent variable will be the post-intervention score (t1), adjusted for its baseline value (t0). Sex and baseline FIQR will be included as prespecified covariates. Results will be reported as adjusted mean differences with 95% confidence intervals. Statistical significance will be set at two-sided p<0.05.

Secondary outcomes will be analyzed using the same ANCOVA framework (t1 adjusted for t0), with Group as the between-subject factor and the same covariates (sex and baseline FIQR). Within-group standardized effect sizes (Cohen’s d) will be presented descriptively.

All analyses will be performed in SPSS v27.0 (IBM Corp., Armonk, NY, USA).

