**4.4 Sample size calculation**

The primary outcome is FIQR. The between-group MCID is ≈14% of the FIQR total score. Assuming SD=20, α=0.05 and power=80% with ANCOVA adjusted for baseline, 32 per group are required (total 64). Allowing 25% attrition, the target sample size is 80.

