**5.3 Timing of Data Processing**

Data will be recorded at two distinct time points (t) throughout the study:

- t₀: Before the intervention
- t₁: Immediately after the intervention

All data will be stored and processed for the strictly necessary duration to complete the study, following these phases:

- **Data Collection and Processing:** Conducted during the intervention period of the study, ensuring that only authorized personnel have access to the information.
- **Storage and Analysis:** Data will be maintained for the time required for analysis and subsequent publication of results, with custody secured through appropriate security measures.
- **Completion and Disposal:** Once the study is concluded and legal retention periods have expired, the data will be anonymized or securely destroyed in accordance with current regulations.

At all times, participants will have the right to access, rectify, restrict, or delete their data as provided by data protection legislation.

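### Section 4.10 describes the primary FIQR model in two incompatible ways; under one of them, reporting the Group effect averaged over Time would halve the estimate

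*Protocol*

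**What the plan says.** Protocol section 4.10 defines the primary FIQR analysis over consecutive sentences.

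- The first names a "two-way repeated-measures ANCOVA with one within-subject factor (Time: t0, t1) and one between-subject factor", the between-subject factor being Group.
- The second states: "The dependent variable will be the post-intervention score (t1), adjusted for its baseline value (t0".
- The third adds: "Sex and baseline FIQR will be included as prespecified covariates".
- The fourth gives the effect measure: "Results will be reported as adjusted mean differences with 95% confidence intervals". It names neither the model term nor the time point to which the difference belongs.

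Section 5.3 confirms that there are no other assessments: "Data will be recorded at two distinct time points (t) throughout the study", namely before and immediately after the intervention.

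Two further places bear on the intent. The sample size section (4.4) reads: "Assuming SD=20, α=0.05 and power=80% with ANCOVA adjusted for baseline, 32 per group are required (total 64". The secondary-outcome sentence in section 4.10 describes its method as the same framework, with the t1 score adjusted for the t0 score and with sex and baseline FIQR as covariates.

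**The concern.** With only t0 and t1, a within-subject Time factor means that both scores are responses. If t1 is the only response, no within-subject factor is left, and t0 belongs on the right-hand side of the model. The first two sentences therefore describe different models, and an analyst or a later analysis plan could claim to follow the protocol with either.

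What is at stake is the size of the reported primary effect. A repeated-measures model offers a Group main effect and a Group×Time interaction, and the protocol does not say which one supplies the adjusted mean difference. The main effect averages over the two time points, one of which precedes treatment. The design benchmark is a between-group MCID ("The between-group MCID is ≈14% of the FIQR total score"), so an estimate on the wrong scale would be set against that benchmark and judged too small.

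**Working it through.** **Inputs**
- From section 4.4: MCID of about 14% of the FIQR total, SD 20, α 0.05, power 80%, 32 per group.
- From section 4.9: FIQR total runs from 0 to 100, higher being worse. I read 14% as 14 points, which is an assumption.
- From section 4.10: two-sided test; covariates sex and baseline FIQR.
- Not in the protocol: the correlation between t0 and t1. I use 0.3, 0.5 and 0.7 as an assumed range. I also assume 10% of participants in one sex category, and complete data at both times.

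**The plan's own figure**

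n per group = 2 × [SD × (z₀.₉₇₅ + z₀.₈₀) / Δ]² = 2 × [20 × (1.960 + 0.842) / 14]² = 32.04.

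This agrees with the stated 32 (33 if rounded up) and supports reading the MCID as 14 points. The sample size does not depend on the point made here.

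**Algebra**

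Let b be the Group coefficient from the ANCOVA of t1 on Group, t0 and sex. Least squares is linear in the response. Regressing t0 on Group, t0 and sex gives a Group coefficient of exactly 0, because t0 is itself a regressor. In a two-level repeated-measures model with t0 and sex as covariates:

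- Group effect averaged over Time: response (t0 + t1)/2, coefficient (0 + b)/2 = b/2.
- Group×Time: response t1 − t0, coefficient b − 0 = b.

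For the average, the residuals and the standard error are halved as well. The confidence interval is therefore halved, while t and p are unchanged. None of this depends on the correlation.

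**One simulated data set** (64 participants, true effect −14, SD 20, correlation 0.5)

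| Quantity | Estimate | 95% CI | t | p |
|---|---|---|---|---|
| ANCOVA on t1 | −13.77 | −22.46 to −5.07 | −3.17 | 0.0024 |
| Group averaged over Time, t0 as covariate | −6.88 | −11.23 to −2.53 | −3.17 | 0.0024 |
| Group×Time, t0 as covariate | −13.77 | −22.46 to −5.07 | −3.17 | 0.0024 |

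Here the halved interval excludes a 14-point difference, while the correct interval contains it.

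**Mean estimates over 4,000 simulated trials at each correlation**

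| Correlation | ANCOVA on t1 | Group averaged over Time | Group×Time |
|---|---|---|---|
| 0.3 | −14.03 | −7.02 | −14.03 |
| 0.5 | −14.04 | −7.02 | −14.04 |
| 0.7 | −13.98 | −6.99 | −13.98 |

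**The case against.** The strongest reply is that the protocol largely settles the matter itself. It names t1 as the dependent variable, it describes the secondary analyses as the same framework with t1 adjusted for t0, and it bases the sample size on a baseline-adjusted ANCOVA. Three statements agree and one conflicts. That stands: the single-response ANCOVA is clearly the probable intent.

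It is also fair that halving takes two steps: the analyst must run the repeated-measures form despite the stated dependent variable, and must then report the Group effect averaged over Time. Group×Time, or the group contrast at t1, gives the full effect. The halving is a conditional consequence, not the expected result.

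A reader might further infer that the primary test loses power. The documents do not support this. Loss of power in the Group main effect would require leaving baseline out of the model, and neither description does so for FIQR; section 4.4 also plans on baseline adjustment. With t0 as covariate, t and p are identical across the three versions.

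Nor does naming baseline FIQR a second time do harm to the primary analysis. It is one covariate and changes no estimate. For the secondary outcomes the separate mention has a purpose, since their own baseline is a different variable.

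The reply does not remove the conflict. The sentence that first names the primary model still specifies one that contradicts the next. This is not a detail left to a statistical analysis plan (none is at hand), because the protocol does fix the model.

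**Conclusion.** The primary model is wrong as written: the repeated-measures description with a Time factor and the single-response ANCOVA cannot both be the analysis when there are two time points. The rest of the protocol points to the ANCOVA.

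The possible damage is confined to the reported estimate and its interval. In the case described, both would be exactly half the t1 effect, so a true difference at the MCID would appear as about 7 points instead of 14. The factor of one half is exact for complete data with t0 as covariate. The figures of 7 and 14 also rest on reading about 14% as 14 points. It would go too far to conclude that the trial will report half its effect, or that its significance test at "Statistical significance will be set at two-sided p<0.05" is weakened.

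**What to change.** In section 4.10, delete the repeated-measures label and the Time factor. State that FIQR at t1 is analysed by ANCOVA with one record per participant and with Group, baseline FIQR (entered once) and sex as terms, and that the Group coefficient with its 95% CI is the primary estimate and the primary test.

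For the secondary outcomes, state the same form with the outcome's own baseline, baseline FIQR and sex.

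This agrees with section 4.4, leaves the sample size unchanged and needs no further data. The cost is rewording a few sentences, which should be done before unblinded data are analysed.

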**4.6 Type of Sampling and Randomization**

Participant recruitment and written informed consent will be obtained by physicians from the “Estilo de vida y salud” research group at CEU Cardenal Herrera University. Randomisation will be conducted by an independent researcher using a computer-generated 1:1 sequence with stratified permuted blocks of random sizes (2–4) within eight strata defined by sex (male/female) and FM severity (four FIQR clusters per Pérez-Aranda et al., 2019 [32]). Allocation will be concealed with sequentially numbered, opaque, sealed envelopes (SNOSE) prepared off-site with tamper-evident seals and carbonless copies. After baseline assessment, site staff will open the next envelope in numerical order to assign the experimental group (EG) or control group (CG). The randomisation list will be held by an independent data manager with no role in enrolment or assessment. Any deviation from sequence or envelope integrity will be recorded and investigated. Outcome assessors and the trial statistician will be blinded to group allocation. Participants and intervention providers cannot be blinded due to the nature of immersive VR and will be instructed not to disclose allocation during assessments. Assessments will be performed by personnel without access to scheduling or allocation logs; groups will be labelled A/B until database lock. Unblinding will occur only to address serious safety concerns or protocol deviations with safety implications, following written authorization from the Principal Investigator; all unblinding events will be logged. The allocation list will remain with the independent data manager.

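### The ANCOVAs adjust for sex and linear baseline FIQR but not for the four-level severity cluster used to stratify randomisation: a minor precision and consistency gap

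*Protocol*

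**What the plan says.** Section 4.6 (Type of Sampling and Randomization) sets a 1:1 allocation in permuted blocks of 2 to 4 within "eight strata defined by sex (male/female) and FM severity". Severity has four levels, described as FIQR clusters. The section gives no cut-points or classification rule and refers to a cited study under number 32. Number 32 in the protocol's own bibliography is a trial comparing strengthening with aerobic exercise.

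Section 4.10 (Information on the Proposed Data Analysis) models the t1 FIQR score adjusted for its t0 value and states: "Sex and baseline FIQR will be included as prespecified covariates". Secondary outcomes use the same framework and covariates, each adjusted for its own t0 value as well. No cluster or stratum term is named for any outcome.

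Section 4.9 describes the FIQR as three domains (function 0–30, symptoms 0–50, overall impact 0–20) that sum to a total of 0–100.

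**The concern.** Stratified blocks make the arms more alike on the stratification factors than simple randomisation would. The treatment estimate then varies less from trial to trial, but the model's standard error shows this only if the prognostic content of those factors is in the model. If some of it is missing, the standard error is too large, the interval too wide and the test below its nominal level.

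Sex enters the model exactly as it was stratified. Severity enters as a straight line in the FIQR total rather than as the four-level category. Whether the line is an adequate stand-in depends on what the clusters are. If they are bands of the total, the line carries nearly everything. If they are profiles across the three domains, two people with the same total can fall in different clusters, and the line cannot separate them. The protocol does not say which applies.

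Only precision is at stake, but the plan has little power to spare. Its 32 per group gives almost exactly 80% power before any benefit from baseline adjustment.

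**Working it through.** **The plan's own figure.** Inputs from section 4.4: SD 20, two-sided α 0.05, power 80%, and a difference of 14% of the FIQR total, read as 14 points on the 0–100 scale.

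n per group = 2 × [20 × (1.960 + 0.842) / 14]² = 32.04. Power at 32 per group is 79.96%. The stated 32 reproduces.

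**Residual degrees of freedom.** The target of 80 with 25% loss leaves 80 × 0.75 = 60. Intercept, group, sex and baseline FIQR use 4, leaving 56. A four-level cluster takes 3 more, leaving 53.

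**Size if the cluster adds information.** Let R² be the share of residual variance that the cluster explains beyond sex and linear baseline FIQR. With arms balanced on the cluster:

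- SE ratio k = 1/√(1 − R²)
- actual two-sided error = 2 × [1 − Φ(1.96k)]
- power of a nominal 80% test = Φ(2.80 − 1.96k), where 2.80 = 1.96 + 0.84

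The documents give no R², so this range is an assumption.

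| R² | SE overstated by | Actual error | Power (nominal 80%) |
|---|---|---|---|
| 0% | 0% | 5.0% | 80% |
| 2% | 1.0% | 4.8% | 79.4% |
| 5% | 2.6% | 4.4% | 78.5% |
| 10% | 5.4% | 3.9% | 76.9% |

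These are upper bounds for each R². The formula assumes perfect balance, which incomplete blocks and attrition will disturb.

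**Simulation.** N = 64, eight strata, blocks of 2 or 4, 6,000 runs per scenario. Assumptions not in the documents: baseline mean 60 and SD 20, 10% men, residual SD 16, the cluster definitions and the cluster effects. Attrition was not simulated. Power is for a 14-point difference. Each pair is without / with the cluster in the model.

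| Scenario | Type I error | Mean model SE | Power |
|---|---|---|---|
| (a) Bands of the total, linear outcome | 5.6% / 5.6% | 4.00 / 4.03 | 93.2% / 92.8% |
| (b) Bands of the total, step-shaped outcome | 5.3% / 5.6% | 4.13 / 4.04 | 91.3% / 92.3% |
| (c) Clusters carry ±7 points beyond the total | 3.3% / 4.9% | 4.38 / 4.04 | 89.3% / 92.5% |

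The Monte Carlo standard error of a 5% rate is √(0.05 × 0.95 / 6,000) = 0.28 points. In (a) both models are correctly specified with normal errors, so the true rate is 5% and the 5.6% is simulation noise.

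In (c) the estimate's empirical SD under the planned model is 4.02, so the model SE is too large by 4.38/4.02 = 1.09, about 9%. The formula agrees: ±7 points is a variance of 49 against 256 (16²), so R² = 49/305 = 16% and k = 1.09. At a nominal 80% the formula puts that extreme case at 74.6% power, again as an upper bound on the loss.

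**Cost of the term if it adds nothing.** In (a) the SE ratio is 4.03/4.00, or 1.009 unrounded. At 80% power: Φ(2.80/1.009 − 1.96) = 79.3%. The critical t value moves only from 2.003 to 2.006. The loss is under about 1 point.

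**The case against.** The case for leaving the model alone is substantial, and most of it stands.

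- **Severity is not missing from the model.** The clusters are formed from the FIQR, and the baseline FIQR score is a covariate. A continuous score usually holds more information than a coarse category built from it. A reader might infer that one stratification factor is ignored and that the stratification's precision is lost. The documents do not support that: most or all of the precision is recovered through the score.
- **The secondary outcomes are better protected than they look.** Each is adjusted for its own t0 as well as sex and baseline FIQR. The cluster would have to predict t1 beyond all three.
- **The clearly harmful scenario is assumed.** An effect of ±7 points independent of the total is half the 14-point target difference. Nothing in the protocol supports it, and the label of FM severity does not suggest content unrelated to the severity score. Missing cut-points are not evidence of extra prognostic content.
- **Under the banded, linear reading the added term is very slightly harmful** (92.8% against 93.2% power).

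Two things remain. The protocol fixes its covariates as prespecified, yet does not say that baseline FIQR is meant to stand in for the cluster. It also gives no definition, and no usable reference number, from which a reader could confirm that the total carries the cluster's information.

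**Conclusion.** The mismatch is real: the trial randomises by severity cluster and does not analyse by it. Its consequence is conditional and small. With clusters that are bands of the total and a linear outcome, it makes no material difference. With a step-shaped outcome, it costs about 2% in SE and 1 point of power. If the clusters carry information beyond the linear total, the SE is overstated by 1% to 5% over the assumed range, and by about 9% in the extreme case. Actual error is then 4.8% down to about 3%, with a few points of power lost.

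A reader might infer that the standard errors are invalid or that false positives are inflated. Neither follows. The treatment estimate remains unbiased under randomisation, any error is conservative, and no scenario showed material inflation from leaving the cluster out.

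This is a minor improvement in precision and design consistency, and it does not invalidate the analysis. The sizes rest on assumed R² values, cluster effects, baseline distribution and residual SD, none of which the protocol gives. They also rest on reading section 4.10 as an ANCOVA of the t1 score.

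**What to change.** In section 4.10, keep sex and continuous baseline FIQR, and add the severity cluster as recorded for randomisation as a four-level fixed factor. Do this in the primary and all secondary ANCOVAs. State in section 4.6 how the clusters are assigned and correct the reference number.

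Use main effects of sex and cluster rather than an eight-level stratum term, because the male strata will be small. Among 60 completers, the 3:1 female-to-male ratio quoted in the Introduction implies 60 × 0.25 = 15 men, about 4 per cluster. At an assumed 10% men there would be 6, or 1 to 2 per cluster.

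The cost is one model term using a variable already known before allocation: 3 of about 56 residual degrees of freedom, and under about 1 point of power if the cluster adds nothing. If the investigators prefer the present model, the minimum is a sentence that defines the clusters and says why continuous baseline FIQR stands in for them.

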**5. Data Processing:**

All data processing will comply with the General Data Protection Regulation (RGPD 2016/679) and the Organic Law on Data Protection and Guarantee of Digital Rights (LOPD-DGG).

**5.1 Data Collection and Storage**

Data will be collected in person by trained assessors at t0 and t1. Paper forms will be double-entered into a password-protected electronic database. Personally, identifying information (PII) will be recorded only on consent forms and a separate offline linkage log stored in a locked cabinet. De-identified analysis datasets will be retained and shared per the Data Availability plan (Zenodo DOI), while the linkage log will be destroyed within one month after database lock.

**5.2 Identification of the Data Controller**

**PII will be collected on consent forms and in a separate linkage log kept offline; the research dataset for analysis will be fully de-identified.**

**5.3 Timing of Data Processing**

Data will be recorded at two distinct time points (t) throughout the study:

- t₀: Before the intervention
- t₁: Immediately after the intervention

All data will be stored and processed for the strictly necessary duration to complete the study, following these phases:

- **Data Collection and Processing:** Conducted during the intervention period of the study, ensuring that only authorized personnel have access to the information.
- **Storage and Analysis:** Data will be maintained for the time required for analysis and subsequent publication of results, with custody secured through appropriate security measures.
- **Completion and Disposal:** Once the study is concluded and legal retention periods have expired, the data will be anonymized or securely destroyed in accordance with current regulations.

At all times, participants will have the right to access, rectify, restrict, or delete their data as provided by data protection legislation.

**5.5 Participants Involved in Each Phase**

Study participants will be adults diagnosed with fibromyalgia, selected based on the established inclusion and exclusion criteria. Prior to participation, they will receive a detailed information sheet and will sign an informed consent form after any questions have been addressed.
Continuous monitoring will be ensured to observe any potential adverse effects and to safeguard participant well-being. Moreover, participants may withdraw from the study at any time without repercussions.
This procedure guarantees adherence to ethical and methodological standards, ensuring the validity and security of the study.

**5.6 Locations Where Data Will Be Stored**

Online data will be stored in encrypted Excel files by the principal investigator on one of the research group's computers, secured with a password. Paper records will be kept in a designated locker for this study, which will remain locked.

**6. Ethical Considerations**

This study will adhere to the CONSORT guidelines for Randomized Controlled Trials and will be evaluated by the Ethics Committee of CEU Cardenal Herrera University, ensuring compliance with all necessary ethical directives. In addition, the study will follow the principles outlined in the Declaration of Helsinki (2013) and Good Clinical Practice (GCP) standards, thereby ensuring the respect, safety, and well-being of the participants.

Fibromyalgia is a chronic condition that significantly impacts the quality of life of those affected. Consequently, any therapeutic intervention must be carefully designed to maximize benefits while avoiding unnecessary risks. In this study, both immersive virtual reality (IVR) and therapeutic exercise have been extensively researched and demonstrated to be safe in similar populations. Nevertheless, potential transient effects—such as mild fatigue or slight dizziness related to IVR—will be closely monitored to guarantee participant well-being.

All study subjects will receive detailed information about the objectives, methodology, potential benefits, and risks of the intervention. Informed consent will be obtained prior to participation, ensuring that individuals make a free and fully informed decision. Furthermore, participants will have the right to withdraw from the study at any time without any negative consequences.

Data processing will be conducted in full compliance with the Organic Law on Data Protection and Guarantee of Digital Rights (LOPD-GDD) and the General Data Protection Regulation (RGPD 2016/679), thereby ensuring both confidentiality and anonymity. The data will be securely stored on CEU Cardenal Herrera University’s servers, with access restricted exclusively to the principal investigators. Upon completion of the study, the data will be disposed of in accordance with established security protocols.

